### Randomisation

Eligible participants will be randomised into the CBT+ or TAU+ group using a complete randomisation scheme generated in advance. Specifically, block sizes of variable size (4, 6 or 8) will be used. Random seeds will be generated to ensure allocation concealment and prevent pre-guessing of the allocation sequence at the end of each block. Randomisation will be stratified by baseline Insomnia Severity Index (ISI) scores (≤7, ≥8) and cancer stage (≤2, ≥3). The randomisation scheme was generated and setup in REDCap (Research Electronic Data Capture) by a member of the research staff (BB) who is not involved in recruitment or delivery of intervention and is not the principal investigator. All participants will receive a random identification number, which will be used to link data from the different assessments. All direct identifiers (for example, name, address and telephone numbers) will be stored separately.

#### CBT+ intervention

The CBT+ intervention involves seven time points when materials are delivered across 6 weeks. The intervention will be delivered via: one face-to-face session of up to 75 min, to be conducted at the PMCC in the Chemotherapy Day Unit; one telephone call lasting approximately 20 min; seven emails (one per week that take approximately 15–20 min to read); and one brief telephone call (2–5 min) at the end of the intervention to ask about adverse events.

Intervention components delivered via email use the online software Mailchimp, which provides professional email templates and automates the timing of intervention delivery.

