### Recruitment and consent

Women diagnosed with BC who receive intravenous chemotherapy treatment at the Peter MacCallum Cancer Centre (PMCC) in Melbourne, Australia, will be recruited after diagnosis and prior to the completion of chemotherapy. We have taken several steps to ensure we achieve adequate recruitment and enrolment. The PMCC pharmacy department will generate a report of potentially eligible women identified through their chemotherapy chart. The research team will attend the Chemotherapy Day Unit when each eligible woman has a scheduled appointment and approach women in person, which encourages higher enrolment. Due to the stress associated with BC treatment and the commencement of chemotherapy, women will not be approached during their chemotherapy education session or at their first chemotherapy appointment. Potentially eligible women who show an interest in participating will be provided with information about the study. Should they choose to participate, written informed consent will be obtained. After consenting, women will complete further screening assessments to determine whether they are eligible to participate. We have taken steps to help retention and completion of follow-up. The CBT+ condition was carefully designed to minimise burden (see section below on CBT+ intervention). In the TAU+ condition, we include a mid-point telephone call and emails to maintain engagement.

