#### TAU+ intervention

The control group will receive two emails containing web links to relaxation audio tracks. These emails will be received during the first and third weeks of the intervention. The first relaxation audio consists of abdominal breathing strategies that may assist in calming the mind and relaxing the body. The second audio consists of a progressive muscle relaxation. Both audio tracks are approximately 15 min long and participants are instructed to listen to these audio tracks whenever they feel it could be beneficial. These relaxation tracks were developed by the Australian Cancer Council to assist people in coping with a cancer diagnosis. The audio tracks do not contain any sleep-specific information; instead, they include general relaxation strategies that can be used by participants at any time during the day or night. The control group will also receive a brief telephone call (15 min) during the fourth week of their study to check in with participants and respond to any queries or complaints. After the 3-month follow-up assessment, women in TAU+ will be offered the seven CBT+ email packages. Women are informed during consent that they will be randomised and, if randomised to TAU+, will receive the CBT+ materials after their final follow-up assessment.

Relaxation audio was chosen as a control so that the efficacy of the intervention can be compared to a general relaxation paradigm that may offer benefits for wellbeing and stress reduction but does not specifically target sleep. Furthermore, an active control will reduce the influence of placebo or expectancy effects and ensure that all women who participate in the study receive some effective support. The number of times TAU+ participants open relaxation emails and click on relaxation audio links will be monitored to evaluate participant engagement with the programme. Notably, both groups continue treatment as usual, including any standard management of sleep symptoms from their oncology team or other health care providers.

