### Ethics approval and safety monitoring

The study has received ethics approval from the PMCC Human Research ethics committee, protocol number 17/159. Governance and oversight of the trial will be monitored by two committees, the Steering Committee and the Data and Safety Monitoring Board (DSMB). The Steering Committee comprises the study investigators and a consumer representative. The DSMB comprises two independent researchers, a consumer representative, and two members of the study investigator team. The DSMB will be responsible for monitoring participant safety, data quality, and implementation of the protocol. If any women report severe symptoms of sleep disturbance, depression, or anxiety, we will inform their clinical team and recommend that they seek a referral to a sleep specialist or clinical psychologist. Any women with previously undiagnosed severe psychiatric conditions identified during screening will also be informed and recommended to seek a referral to psychiatry or clinical psychology. A description of all undesirable and unanticipated events during the intervention phase (adverse events) will be recorded on Qualtrics. As this trial is minimally funded, there is no independent audit. Any protocol modifications will be communicated to the Human Research ethics committee and participants by the study team. No serious harm is expected as a result of the trial. However, if harm does occur, the primary sponsor and Monash University insurance will cover care for research participants.

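### Only the CBT+ arm is described as having an end-of-intervention call that asks about adverse events, so any count of harms by arm is at risk of ascertainment bias

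*Protocol article*

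**What the plan says.** The section on the CBT+ intervention lists that arm's contacts: a face-to-face session of up to 75 minutes, a telephone call of about 20 minutes, seven emails, and a further call of 2–5 minutes "at the end of the intervention to ask about adverse events".

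The section on the TAU+ intervention describes two emails linking to relaxation audio, sent in weeks 1 and 3, and one 15-minute call "during the fourth week of their study to check in with participants and respond to any queries or complaints". Recruitment and consent gives the purpose of these contacts: "In the TAU+ condition, we include a mid-point telephone call and emails to maintain engagement".

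Ethics approval and safety monitoring sets the standard for the whole trial: "A description of all undesirable and unanticipated events during the intervention phase (adverse events) will be recorded on Qualtrics". It adds: "The DSMB will be responsible for monitoring participant safety, data quality, and implementation of the protocol". Neither sentence is confined to one arm, and neither says how events are to be elicited. Study design states that the trial is not blinded.

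**The concern.** How many adverse events are recorded depends on how and when women are asked. As described, one arm gets a direct question at the end of the six weeks. The other gets a general check-in about two weeks before the end, which cannot reach anything that happens afterwards. CBT+ also has more personal contact during which events might be volunteered.

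The women are receiving chemotherapy, and the Background names symptoms that go with it, such as nausea, hot flushes and pain. Some unwelcome events will occur in both arms whatever the allocation, so a count in CBT+ can be interpreted only against a control count obtained in the same way. If the enquiry differs by arm, CBT+ may look less safe than it is, and late events in TAU+ may be missed.

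**Working it through.** The documents give no figure for adverse events, so there is nothing to reproduce. The check has two parts.

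**1. The arms side by side, as described**

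- *Contact with the stated purpose of asking about adverse events:* CBT+ has one, of 2–5 minutes; none is described for TAU+.
- *Timing of the last described telephone contact with staff, apart from questionnaires:* end of the intervention in CBT+; week 4 in TAU+.
- *Stated purpose of that contact:* adverse events in CBT+; check-in, queries or complaints, and engagement in TAU+.
- *Contacts common to both arms:* self-report questionnaires at weeks 0, 3, 6 and 12, online or by telephone (Assessments and outcomes). The text does not say whether they include an adverse-event item, and Table 1 is not shown.
- *Recording:* Qualtrics, not limited to one arm.

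The arms differ in both the timing and the directness of the enquiry. The only contact near week 6 that they share is the questionnaire, whose adverse-event content is not stated.

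**2. What unequal detection would do (illustration; the inputs are assumptions, not figures from the documents)**

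Let *p* be the true proportion of women with a reportable event, equal in both arms, and let *s* be the probability that such an event is recorded.

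Recorded proportion = *p* × *s*

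Apparent risk ratio = (*p* × *s*_CBT+) / (*p* × *s*_TAU+) = *s*_CBT+ / *s*_TAU+

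Apparent risk difference = *p* × (*s*_CBT+ − *s*_TAU+)

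Take *s*_CBT+ = 1.0 and vary *s*_TAU+:

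- *s*_TAU+ = 0.5: risk ratio 1/0.5 = 2.00
- *s*_TAU+ = 0.7: risk ratio 1/0.7 = 1.43
- *s*_TAU+ = 0.9: risk ratio 1/0.9 = 1.11
- *s*_TAU+ = 1.0: risk ratio 1.00

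The risk ratio does not depend on *p*, but the risk difference does. For *s*_TAU+ of 0.5, 0.7 and 0.9 in turn:

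- *p* = 10%: 5, 3 and 1 percentage points
- *p* = 20%: 10, 6 and 2 percentage points
- *p* = 30%: 15, 9 and 3 percentage points

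In women: 101 were randomised (Trial status), so about 50 per arm. At *p* = 20%, CBT+ would record 50 × 0.20 = 10 women with an event. TAU+ would record 10 × 0.5 = 5, 10 × 0.7 = 7 or 10 × 0.9 = 9. The true difference is zero throughout.

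**The case against.** There is a good deal to say on the other side.

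- **No comparison of harms is planned.** Adverse events are not among the primary or secondary outcomes, and the statistical section has no between-arm test of them. A reader might infer that a planned safety comparison is biased; the article does not support that, because it contains no such comparison. What stands is conditional: if events are tabulated by arm, or if the safety board reviews them by arm, the counts inherit the unequal enquiry.
- **TAU+ events may still be captured.** Recording on Qualtrics is not limited to one arm, both arms complete a week-6 questionnaire, and the week-4 call invites complaints. A reader might infer that late events in TAU+ go unrecorded; the documents do not establish that. However, the safety section says where events are recorded, not how they are sought. Even if both arms answer a questionnaire item, CBT+ would have one active enquiry more.
- **The article is condensed.** The full protocol is a separate document, and an equivalent enquiry in TAU+ cannot be ruled out. This limits confidence. But the point does not rest on silence alone: the article describes the contacts of both arms and names a safety call in only one.
- **Expected effects of chemotherapy may not count.** The definition covers events that are both undesirable and unanticipated, so the background rate of qualifying events could be low. That would shrink the absolute difference but leave the ratio unchanged.
- **It is late.** Recruitment ended in October 2019 and this version is dated 18 November 2019. Six weeks (42 days) before that date is 7 October, so only women who started after about then were still short of week 6. An added call could therefore reach few TAU+ women; the reporting remedy could still be applied in full.

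**Conclusion.** The point holds in a limited form. As described, adverse events are actively asked about at the end of the intervention in CBT+ only, although the plan intends to record them without distinction between arms. Any count of harms by arm is therefore at risk of ascertainment bias, probably making CBT+ look worse.

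The size cannot be fixed from the documents. The apparent risk ratios of 1.11 to 2.00 rest on three assumptions: equal true risk, full detection in CBT+, and 50% to 90% detection in TAU+. If detection is in fact equal, there is no bias. The primary and secondary efficacy analyses and the sample size do not depend on this. It is worth correcting because the remedy is cheap, but it does not threaten the trial's main result.

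**What to change.** For women not yet past week 6, ask the same scripted adverse-event question at that point in both arms, either by the same 2–5 minute call or within the week-6 assessment. State in the protocol that this is done. If TAU+ women are already asked in the same way, one sentence saying so resolves the point.

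For women already past week 6, compare arms only on adverse-event sources that were applied identically. List separately the events found only through the CBT+ call, and report how each arm was asked.

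The cost is a few minutes of staff time and one more brief contact for each remaining TAU+ woman, plus a line in the protocol. The restriction to common sources leaves fewer events in the comparison by arm; the separate listing keeps the others visible.

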##### Cognitive behavioural therapy for insomnia

The intervention materials for the CBT component were adapted from the *Cognitive behavioural treatment of insomnia: a session by session guide* [52]. Core components of the intervention content include:
General information and skills for better sleep (for example, sleep hygiene, relaxation and mindfulness exercises, dealing with night-time worries)Fostering healthy attitudes and expectations about sleep following cancer diagnosis and during treatmentManaging sleep challenges specific to cancer patients (for example, physical discomfort, pain, daytime consequences of poor sleep)Identifying and managing symptoms of insomnia (for example, self-monitoring, stimulus control, sleep scheduling, bed restriction)

The CBT face-to-face session will be delivered by [name], a provisional psychologist and doctoral graduate student who has completed >450 h of clinical client contact and an additional 40 h of specific CBT-I training. [name] will be supervised by senior clinical psychologists JD and BB.

##### Light therapy individualised protocol

The light therapy component will consist of daily use of light glasses for the 6-week duration of the intervention. Participants will receive a pair of Luminette® glasses with light intensity locked at 1500 lux and will be instructed to wear them for 20–30 min after awakening each morning. The specific timing of use will be established with each participant during the face-to-face session, and will be based on their individual sleep–wake timing and chronotype, accounting for early awakenings. A written light therapy manual covers the key components to be discussed in the face-to-face session.

##### Minimising participant burden

The intervention was designed to deliver effective results while being of minimal burden. Given that women with BC already have an intensive treatment regimen, the design of the intervention was carefully considered, weighing the physical and psychological benefits with the effort and time associated with each intervention component. The face-to-face session will be scheduled around participants’ existing appointments to reduce the burden of travel. All other aspects of the intervention can be completed in the comfort of the participants’ own homes. The light glasses are comfortable, easy to wear, and can be worn over prescription eyeglasses. Outside of morning showers, vigorous exercise, or driving, the light glasses are not likely to disrupt participants’ usual morning routines. Wearing the light glasses will not impair participants’ ability to move around and undertake any domestic or work-related responsibilities (such as preparing and consuming food, household cleaning, reading, writing or typing). Furthermore, the intervention is economical from the perspective of the health care system as it is relatively simple for clinicians to deliver and entails minimal financial expense and burden of time. These are important considerations when evaluating whether the intervention, if effective, could be implemented into routine care.

#### TAU+ intervention

The control group will receive two emails containing web links to relaxation audio tracks. These emails will be received during the first and third weeks of the intervention. The first relaxation audio consists of abdominal breathing strategies that may assist in calming the mind and relaxing the body. The second audio consists of a progressive muscle relaxation. Both audio tracks are approximately 15 min long and participants are instructed to listen to these audio tracks whenever they feel it could be beneficial. These relaxation tracks were developed by the Australian Cancer Council to assist people in coping with a cancer diagnosis. The audio tracks do not contain any sleep-specific information; instead, they include general relaxation strategies that can be used by participants at any time during the day or night. The control group will also receive a brief telephone call (15 min) during the fourth week of their study to check in with participants and respond to any queries or complaints. After the 3-month follow-up assessment, women in TAU+ will be offered the seven CBT+ email packages. Women are informed during consent that they will be randomised and, if randomised to TAU+, will receive the CBT+ materials after their final follow-up assessment.

Relaxation audio was chosen as a control so that the efficacy of the intervention can be compared to a general relaxation paradigm that may offer benefits for wellbeing and stress reduction but does not specifically target sleep. Furthermore, an active control will reduce the influence of placebo or expectancy effects and ensure that all women who participate in the study receive some effective support. The number of times TAU+ participants open relaxation emails and click on relaxation audio links will be monitored to evaluate participant engagement with the programme. Notably, both groups continue treatment as usual, including any standard management of sleep symptoms from their oncology team or other health care providers.

### Assessments and outcomes

Table 1 displays the measurements used in this study and the time points at which they will be administered. Screening interviews will be conducted in person during recruitment prior to randomisation. Baseline (week 0), mid-treatment (week 3), post-treatment (week 6), and 3-month follow-up (week 12) questionnaires with self-report measures will be completed online by emailing women a link to a survey on Qualtrics, or via telephone for women who prefer not to complete questionnaires online. Questionnaires completed via Qualtrics will be considered valid if they are completed within ±1 week of the planned time.

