## Method

### Study design

This is a randomised, two-group, parallel, non-blinded, controlled, single-centre, superiority trial. One group will receive combined CBT plus BLT (CBT+). The other group will receive treatment as usual enhanced with a relaxation audio programme serving as an active control (TAU+). All participants will be involved in the trial for the 6-week duration. Measures will be taken at baseline, at the mid-point of the intervention (3 weeks) and post-treatment (6 weeks). A follow-up assessment will occur at 3 months to evaluate any sustained effects of the intervention on primary and secondary outcomes. This trial and protocol adhere to SPIRIT [48] and TIDieR [49] recommendations.

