#### Baseline comparisons

Participant characteristics at baseline will be presented by treatment group, and statistical tests will be conducted to verify that randomisation was successful. Discrete variables will be summarised by frequencies and percentages, and baseline group differences tested using chi-square tests. Continuous variables will be summarised using mean (standard deviation) or median (interquartile range) and baseline group differences, tested using independent *t* tests or Wilcoxon signed-rank tests for variables that evidence non-normal distributions. If there are significant differences in any participant characteristics at baseline, the variable(s) will be included as covariates in the final analyses.

#### Aim 1

Aim 1 is to test the efficacy of CBT+ compared to TAU+ for improving symptoms of sleep disturbance. Aim 1 will be tested using LGMs. LGMs will be estimated with an intercept and two linear slopes, representing a piecewise model. Slope 1 will have loadings constrained to 0, 0.5, 1.0 and 1.0 for weeks 0, 3, 6 and 12, respectively, capturing the linear change from baseline (week 0) to post-intervention (week 6). Slope 2 will have loadings constrained to 0, 0, 0 and 1.0 for weeks 0, 3, 6 and 12, respectively, allowing a different slope from post-intervention (week 6) to follow-up (week 12) compared to from baseline (week 0) to post-intervention (week 6). The means and variances of the intercept and slope factors will be freely estimated (corresponding to random effects in linear mixed models) and the intercept and slope covariances will be estimated. The residual variance will be constrained to equality across time and residuals assumed uncorrelated, corresponding to an independent, homogenous residual structure. Intercepts of indicators will be constrained to 0 to allow estimation of the latent random intercept mean.

There are two stratification factors: screening ISI (≤7, ≥8) and cancer stage (≤2, ≥3). These factors will be crossed, creating four groups: early-stage, low ISI; advanced-stage, low ISI; early-stage, high ISI; and advanced-stage, high ISI. Dummy codes will be created for each strata, with early-stage, low ISI treated as the reference group. These dummy codes will be included as covariates to adjust for their effect on the random intercept following recommendations that stratification factors be adjusted for in analyses of randomised controlled trials [76, 77].

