Treatment effects will be evaluated by creating a dummy code (0 = TAU+, 1 = CBT+). This dummy code will be entered as a predictor of the intercept, slope 1 and slope 2. However, treatment factors will be constrained to 0 for the intercept, to implement so-called constrained longitudinal data analysis, which studies show provides a more accurate estimate of treatment effects from randomised controlled trials with repeated measures [78, 79].

The primary trial results will be the effect of treatment on slope 1 (i.e. from week 0 to week 6). This interaction directly tests whether the change in primary outcomes over time is different in the control and intervention arm. Effect sizes of the group difference at each time point also will be calculated.

A similar process will be followed for sleep efficiency; however, a continuous time, linear model will be estimated using a mixed effects model in Mplus because up to 42 days of sleep efficiency are collected. A piecewise model is not needed as sleep diary data are not collected at follow-up due to burden. Sleep efficiency may not follow a normal distribution. If the assumption of normality is violated, significance tests and confidence intervals will be based on non-parametric bootstrapping.

#### Aim 2

Aim 2 is to test the efficacy of CBT+ versus TAU+ for psychological outcomes. Aim 2 will be tested identically to aim 1, but using psychological outcomes in place of the sleep and fatigue outcomes.

#### Aim 3

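### The ±1 week validity window also covers week 0, so a questionnaire completed after allocation and early in open-label treatment can count as baseline

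*Protocol article*

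**What the plan says.** Assessments and outcomes places one activity before allocation: "Screening interviews will be conducted in person during recruitment prior to randomisation". It then describes the questionnaires: "Baseline (week 0), mid-treatment (week 3), post-treatment (week 6), and 3-month follow-up (week 12) questionnaires with self-report measures will be completed online", with telephone completion as an alternative. The validity rule follows: "Questionnaires completed via Qualtrics will be considered valid if they are completed within ±1 week of the planned time". It is symmetric and makes no exception for week 0.

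Study design describes the trial so: "This is a randomised, two-group, parallel, non-blinded, controlled, single-centre, superiority trial". It also gives the clock: "Measures will be taken at baseline, at the mid-point of the intervention (3 weeks) and post-treatment (6 weeks".

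The stratifying ISI has two names. Under Randomisation: "Randomisation will be stratified by baseline Insomnia Severity Index (ISI) scores (≤7, ≥8) and cancer stage (≤2, ≥3". Under Statistical analyses, Aim 1: "There are two stratification factors: screening ISI (≤7, ≥8) and cancer stage (≤2, ≥3".

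The Aim 1 model gives week 0 a slope 1 loading of 0, by planned week. On the treatment indicator it says: "treatment factors will be constrained to 0 for the intercept". The effect of treatment on slope 1 is the primary result.

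**The concern.** A constrained-baseline model needs a baseline that allocation cannot have affected. Randomisation guarantees this only for a measurement taken before the woman knows her arm and before treatment begins. A window that runs to one week after week 0 lets in scores that may already carry some treatment effect, or a reaction to the arm received. The model still scores them as time 0 and sets the arm difference there to zero.

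The scores concerned are self-reported and the trial is open-label. An early benefit in a late baseline would shrink the slope 1 effect; a reaction to allocation could bias it either way. The mechanism analyses under Aim 3 are more exposed, because they use change from baseline to the treatment mid-point. With a symmetric window at both ends, that change could span 7 days instead of 21.

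**Working it through.** **1. Does the window reach past allocation?** Week 3 is the mid-point of the intervention and week 6 is post-treatment. Counting back, week 0 is in effect the start of the intervention. This is an inference, as the article does not define the planned time for week 0. On that clock, a questionnaire completed on day +7 is valid as baseline.

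**2. Which scores are exposed?**
- *PROMIS and mechanism scores:* nothing in the text shown requires completion before allocation.
- *ISI:* a score that defines the randomisation stratum must exist before allocation. If it is also the analysed week-0 ISI, the ISI baseline is safe in practice, but the window then contradicts the Randomisation section. If the screening ISI is a separate measurement, the analysed week-0 ISI is exposed. The text does not settle which.
- *Diary sleep efficiency:* collected on paper diaries, so this window does not govern it.

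**3. The plan's own power figure.** Inputs from Sample size and power: 70 women, d = 0.70, α = 0.05, independent-samples t test. I assume 35 per arm and a two-sided test. The noncentrality is 0.70 × √(35/2) = 2.93. Power is 82.3% from the noncentral t distribution and 83.4% from the normal approximation. The stated figure of more than 80% is reproduced. The test compares post-treatment scores only, so baseline timing does not enter it.

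**4. How much could a late baseline absorb?** Slope 1 is linear from week 0 to week 6, so one week carries 1/6 of the week-6 effect: 0.70/6 = 0.117. Let f be the share of CBT+ baselines a full week late, and ρ the correlation between baseline and week 6. A baseline-adjusted estimate is then approximately

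d × (1 − ρ × f / 6).

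This approximates the latent growth model; ρ = 1 corresponds to a raw change score. The article gives neither f nor ρ, so all values below are assumptions. Cells show the effect that d = 0.70 would appear as, with the attenuation.

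| f | ρ = 0.3 | ρ = 0.5 | ρ = 0.7 | ρ = 1.0 |
|---|---|---|---|---|
| 0.25 | 0.691 (1.3%) | 0.685 (2.1%) | 0.680 (2.9%) | 0.671 (4.2%) |
| 0.50 | 0.682 (2.5%) | 0.671 (4.2%) | 0.659 (5.8%) | 0.642 (8.3%) |
| 1.00 | 0.665 (5.0%) | 0.642 (8.3%) | 0.618 (11.7%) | 0.583 (16.7%) |

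A front-loaded response would put more than 1/6 of the effect into the first week.

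**5. Mechanism interval.** Planned: day 21 − day 0 = 21 days. Shortest valid: (21 − 7) − (0 + 7) = 7 days.

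**The case against.** The strongest reply concerns ISI. Randomisation is stratified on baseline ISI, and Aim 1 gives the same cut-offs under the name screening ISI. The plainest reading is one measurement, taken before allocation, under two labels. This stands: the documents do not show that the analysed ISI is taken after treatment starts, and a reader should not infer it. What remains for ISI is an inconsistency of wording that leaves a second measurement possible.

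It can also be said that Table 1 and the flow chart are not shown, that a full protocol exists elsewhere, and that the planned time for week 0 is not tied to treatment start. The face-to-face session is scheduled around existing appointments, so its distance from the questionnaire is not fixed. These are fair limits on how far the window reaches in practice. They do not remove the point, which concerns a rule the article states and not a detail it omits. The rule covers week 0 as worded, and nothing shown narrows it.

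A reader might also infer that power falls from 82% to 67%. The 67.2% is the power at d = 0.583 with 35 per arm, which needs every CBT+ baseline a full week late and a raw change score. The planned t test does not use baseline at all, and the planned model is not a raw change score. In addition, 101 women were randomised and the analysis is by intention to treat, so 35 per arm is not the final sample. The fall does not describe this trial's planned power.

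**Conclusion.** The point holds as an inconsistency in a stated rule and should be corrected before analysis. As worded, the window admits a week-0 questionnaire completed after allocation and up to a week into open-label treatment. That is incompatible with the zero treatment effect on the intercept and the time-0 loading, and with stratification on baseline ISI if that is the same score. It bears mainly on the PROMIS outcomes and the mechanism scores, and on ISI only if the screening and week-0 ISI are separate measurements.

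The bias may be small: about 1% to 17% attenuation over the assumed values, with 1/6 as the ceiling under linear accrual. This rests on week 0 being treatment start and on unknown values of f and ρ. The case for the correction rests on the validity of the baseline, not on the worst-case figure.

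**What to change.** Limit the ±1 week window to weeks 3, 6 and 12. Count a week-0 questionnaire as baseline only if it was completed before the arm was disclosed and before any arm-specific material or treatment, preferably before randomisation. State that the analysed week-0 ISI is the pre-randomisation ISI used for stratification, and use one name for it throughout. If two ISI administrations exist, say so and report the interval between them, because the earlier one is not exactly at week 0.

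Recruitment is complete, so apply the rule through completion, randomisation and treatment-start dates. Treat week-0 scores completed after disclosure or treatment start as missing in the likelihood model, and report how many there are by arm. Setting every post-randomisation questionnaire to missing would be broader than needed. Fix the rule before results are examined, since the statisticians are not blinded.

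The cost is a sentence or two in the protocol and a date check on records already held. The downside is that some week-0 PROMIS or mechanism scores may become missing. Their number cannot be known from the article, and the mechanism change scores would feel the loss most.
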